## Abstract

**Background:**

Estimates of the risk of developing Crohn's disease (CD) can be made using DNA testing for mutations in the NOD2 (CARD15) gene, family history, and smoking status. Smoking doubles the risk of CD, a risk that is reduced by stopping. CD therefore serves as a timely and novel paradigm within which to assess the utility of predictive genetic testing to motivate behaviour change to reduce the risk of disease. The aim of the study is to describe the impact upon stopping smoking of communicating a risk of developing CD that incorporates DNA analysis. We will test the following main hypothesis:

Smokers who are first degree relatives (FDRs) of CD probands are more likely to make smoking cessation attempts following communication of risk estimates of developing CD that incorporate DNA analysis, compared with an equivalent communication that does not incorporate DNA analysis.

**Methods/design:**

A parallel groups randomised controlled trial in which smokers who are FDRs of probands with CD are randomly allocated in families to undergo one of two types of assessment of risk for developing CD based on either:

i. DNA analysis, family history of CD and smoking status, or

ii. Family history of CD and smoking status

The primary outcome is stopping smoking for 24 hours or longer in the six months following provision of risk information. The secondary outcomes are seven-day smoking abstinence at one week and six month follow-ups. Randomisation of 470 smoking FDRs of CD probands, with 400 followed up (85%), provides 80% power to detect a difference in the primary outcome of 14% between randomised arms, at the 5% significance level.

**Discussion:**

This trial provides one of the strongest tests to date of the impact of communicating DNA-based risk assessment on risk-reducing behaviour change. Specific issues regarding the choice of trial design are discussed.

**Trial Registration:**

ISRCTN: ISRCTN21633644

## Background

There are high expectations regarding the potential for estimates of disease risk incorporating DNA analysis to motivate behaviour change more strongly than other types of risk information [1,2]. Such expectations are consistent with theories of attitude change which predict that the greater the personal salience of information, such as information regarding one's own DNA, the greater the impact [3]. We present here a protocol for a randomised controlled trial assessing the behavioural impact of using DNA analysis to estimate disease risk. This DNA analysis will be used to quantify the susceptibility to Crohn's disease (CD) of smokers who are first degree relatives (FDRs) of probands with CD, a susceptibility that is modifiable by smoking cessation. The behavioural effect of communicating the results of the analysis will be measured by the proportion of smokers who report stopping for 24 hours or longer in the six months following the provision of the risk assessment.

CD is a relatively common, complex genetic condition with a population prevalence of around 1 per 1000 per lifetime [4] and first degree relatives (FDRs) have an approximately twenty-fold increased risk of developing the condition [5]. Results from recent epidemiological and genetic studies now make it possible to offer relatives of probands increasingly precise information about their chances of developing the disease, using DNA analysis of the NOD2 genotype [5,6].

Smoking is an additional risk factor and is associated with a two-fold increase in the risk of developing CD [7]. Smoking also leads to a more aggressive course in those with the disease [8,9]. Importantly, this pattern is reversed by smoking cessation [10].

As can be seen from Table 1 the relative risks for NOD2 mutations in CD are much lower than the risks for highly penetrant mutations in single gene disorders. However, they are higher than most other mutations associated with complex disorders. In those who are NOD2 mutation-negative the lifetime absolute risk of developing CD is very low (approximately 2% in first degree relatives; see Lewis et al [5]). Since commercial testing is currently being offered for a range of common, complex disorders with the expectation of motivating behaviour to reduce risk (e.g. 23 and Me https://www.23andme.com/; Navigenics http://www.navigenics.com/ predictive testing for CD serves as a timely and novel paradigm in which to assess the impact of communicating the results of predictive genetic testing in motivating risk-reducing behaviour change, in this case smoking cessation. A series of genome-wide association scans in CD have recently identified multiple new susceptibility genes and loci (reviewed by Mathew [11]). In most cases, however, the associations have been detected with single nucleotide polymorphisms (SNPs) that tag common haplotypes at these loci. Since most of the causal genes or causal sequence variants have not yet been clearly defined, the precise degree of additional genetic risk that they confer is unknown.

**Table 1 T1:** Estimated frequencies of NOD2 genotypes in probands and FDRs, and estimated FDRs' probability of developing CD.

	NOD2 mutation negative	NOD2 mutation heterozygous	NOD2 mutation homozygous
**Frequency of NOD2 genotype in CD probands**	65%	27%	8%

**Frequency of NOD2 genotype among FDRs**	75%	22%	3%

**Frequency of NOD2 genotype in controls**	87%	12%	1%

**Risk to FDRs of developing CD conferred by genotype**	2%	4%	15%

We are unaware of any previous attempt to provide relatives of probands with CD with information that might encourage them to engage in behaviours to reduce their risks of developing the condition. Of interest is whether providing precise and personalised DNA-based information about the likelihood of developing Crohn's disease and how such a likelihood might be reduced leads to smoking cessation. Two studies have evaluated the impact of DNA-based risk information of developing lung cancer on smokers' motivation to stop smoking. Both used a general population sample [12-14]. While the first of these provided evidence of increased motivation to stop smoking [12,13], the other did not, with over 50% of smokers in the study failing to understand or recall their DNA test results [14]. Neither study found that DNA-based risk information increased smoking cessation.

There is some evidence to suggest that when DNA analyses reveal no risk-enhancing mutations there may be higher levels of false reassurance and hence lower rates of risk-reducing behaviour than similar levels of risk estimated without DNA analyses [15,16]. Such an effect may follow from presenting the results of the analysis of a risk factor that is personally salient and perceived as categorical *i.e*. the mutation is either present or it is not, although the risk it confers is most often probabilistic. We therefore predict that those whose risk analysis includes DNA but for whom no risk-enhancing mutations are found will be less likely to make a quit attempt than those whose risk analysis did not include DNA analysis. Additionally, we predict a dose-response effect of the receipt of DNA-based risk information: individuals who are revealed to have one or more risk-enhancing mutations will be more motivated to change their behaviour than those who receive a DNA-based risk revealing no mutations, or those in the comparison arm who did not undergo DNA analysis.

### Objective and hypotheses

The trial objective is to estimate the impact upon stopping smoking of communicating a risk of CD that incorporates DNA analysis. The specific hypotheses to be examined are as follows:

#### Hypothesis I (Main hypothesis)

Smokers who are FDRs of CD probands are more likely to make smoking cessation attempts following communication of risk estimates of developing CD that incorporate DNA analysis, compared with an equivalent communication that does not incorporate DNA analysis (between arm comparison).

#### Hypothesis II

Among smokers whose CD risk assessment includes feedback of DNA analysis, smoking cessation attempts are more likely when the analysis reveals one or more risk increasing mutations, when compared with (a) those undergoing a similar DNA analysis that does not reveal any risk increasing mutations (any versus no mutation; within DNA arm comparison), (b) risk assessment that does not incorporate DNA analysis (any mutation versus non-DNA arm).

#### Hypothesis III

Among smokers whose CD risk assessment includes feedback of DNA analysis, smoking cessation attempts are less likely when the analysis does not reveal any risk increasing mutations, when compared with smokers receiving a risk assessment that does not incorporate DNA analysis (no mutation versus non-DNA arm).

## Methods/Design

### Trial design (*see *Figure 1)

**Figure 1 F1:**
[figure not shown]
**Trial design**.

A parallel group cluster randomised controlled trial in which smokers who are first degree relatives of probands with Crohn's disease will receive the results of one of two types of risk assessment for developing Crohn's disease, based on:

i. DNA testing for NOD2 genotype, family history of CD and smoking status, or,

ii. family history of CD and smoking status

### Participants

Participants will comprise 470 FDRs of probands with CD, aged 18 years and over, who do not have a diagnosis of CD or ulcerative colitis and who smoke five or more cigarettes daily. Participants must be able to give informed consent and to complete, either alone or with assistance, the study questionnaires.

Exclusion criteria:

1. Cigar, pipe and oral tobacco users who do not also smoke five or more cigarettes daily.

2. Those currently taking medication for smoking cessation or medication with a known influence on smoking cessation that they cannot stop (e.g. nortriptyline for depression).

3. Those who are non-English speakers.

### Interventions

The components of the interventions described below are shown in Table 2.

**Table 2 T2:** Intervention components present in DNA and non-DNA risk assessment arms

Intervention component	DNA arm	Non-DNA arm
Mouthwash posted to participant to collect saliva sample for NOD2 Genotyping	√	X

Booklet containing results of risk assessment posted approximately 6 weeks after initial contact	√	√

Personal risk presented using a numerical risk with a denominator of 1000, accompanied by a visual display	√	√

Feedback of risk assessment based on family history of CD and smoking Status	√	√

Feedback of risk assessment based on NOD2 genotype	√	X

Explanation of NOD2 gene in booklet	√	X

Explanation of how stopping smoking reduces the risk of CD in booklet	√	√

Smoking cessation advice over the telephone	√	√

#### Communication of risk assessment for Crohn's disease

All participants will receive a booklet outlining the results of their risk assessment of developing CD. This comprises presentation of three lifetime risk figures: population risk (1:1000); personal risk, presented numerically with a denominator of 1000 and accompanied by a visual display [17]; and personal risk following smoking cessation. The booklet includes explanations of how the risk figure was estimated and of how stopping smoking reduces the risk of CD. The nature of the risk assessment differs by arm and risk estimates are calculated as follows:

#### Comparison (non-DNA) arm

Personal risks of developing CD are based on residual familial risk i.e. whether the proband is a parent, sibling or child (estimating the effect of unidentified genes, after accounting for the contribution of NOD2); and smoking status (two-fold increased risk for smokers), as described in previous research [5].

#### Intervention (DNA) arm

Personal risks of developing CD are again based on residual familial risk and smoking status, plus NOD2 genotype (conferring a gene dosage effect on risk) derived from a mouthwash sample returned by the participant, again calculated according to prior research [5]. In effect, the risk communicated to the DNA arm is calibrated into high, medium and low, whilst the control arm receive an "averaged" genetic risk, based on their family history. DNA will be extracted and analysed for known NOD2 (also known as CARD15) susceptibility mutations (*see Procedure for more details*).

#### Brief smoking cessation advice

Receipt of the results booklet is followed by a telephone call (see "Telephone call 2" in Procedure) from a research counsellor trained as an NHS Stop Smoking Service provider who goes over the information in the booklet to ensure comprehension and to deliver a brief smoking cessation intervention. This is aimed at increasing motivation to stop smoking and in those motivated to stop, to encourage use of the NHS Stop Smoking Services.

### Procedure

#### Participant recruitment

First degree relatives of people affected by Crohn's disease will be identified via three routes:

i. Probands receiving care through hospital services. Proband addresses will be obtained by gaining accesses to CD proband databases at participating hospitals, following the approval of the local hospital Trust Research and Development department. Probands may be given study invitation packs or telephoned by members of the clinical team.

ii. Probands who are members of the National Association for Colitis and Crohn's Disease (NACC). All members who have CD will be posted an invitation pack.

iii. Advertising in the newsletters of NACC and the charity Ostomy Lifestyle.

Probands will be posted a study information booklet and consent form. They will be asked to inform any FDRs of theirs who smoke and who are unaffected by CD or ulcerative colitis about the study. They will be asked to indicate on the consent form their preferred method for the study team to contact their relatives, either requesting the study information from the research team in order to give this to their relatives themselves, or providing their relatives' contact details, for the research team to make the contact. This procedure was developed as part of a feasibility study for this trial [18].

Information booklets and consent forms will be distributed to identified FDRs. Eligible FDRs who have read and understood the study information booklet will sign and return the consent form to the research team at KCL. The research counsellor will then telephone the participant and obtain further verbal consent before entering them into the trial.

#### Telephone call 1

Information will be collected about the participant's family history of CD to contribute to the risk assessment, as well as demographic and smoking characteristics. The participant's date of birth will be noted for randomisation at a later date.

Participants will be randomised after Telephone call 1. Those randomised to the DNA arm will be asked to provide a saliva sample for a DNA test. Non-DNA arm participants will not undergo a DNA test and hence will not be asked to provide a saliva sample. The trial co-ordinator will then send the results booklet to the participant (see *Communication of risk assessment for Crohn's disease*).

#### Telephone call 2

Following receipt of the results booklet, the research counsellor will telephone the participant to administer the brief smoking cessation intervention as previously described.

#### Telephone call 3

A member of the research team who did not deliver the intervention will assess self-reported seven-day smoking cessation approximately one week after telephone call 2 has taken place.

#### Telephone call 4

This will take place six months after the second telephone call to assess the primary endpoint, seven-day smoking cessation, and levels of worry caused by the risk assessment. This telephone call will be made by a member of the research team who did not deliver the intervention and who is blind to allocation. Saliva samples will be collected via post in those who report seven day smoking abstinence, to allow cotinine validation.

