#### Secondary cessation outcomes

##### Seven-day smoking cessation at one week

Self-reported smoking cessation will be assessed at one week following receipt of the CD risk assessment.

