##### Seven-day smoking cessation at six months

At six months abstinence from smoking in the preceding seven days will be assessed using the Russell standard procedures [21], counting participants lost to follow up as being smokers, and self-reported smoking status will be verified biochemically. Validated abstinence requires smoking no more than 5 cigarettes in the prior seven-day period and a cotinine level of <15 ng/ml.

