##### Additional outcomes

Questionnaires administered within telephone calls 1,3 and 4 will assess key variables derived from three psychological theories, specifically Leventhal's self-regulation model of health and illness [22], Protection Motivation Theory [23], and the Theory of Planned Behaviour [24]. We will also assess self-reported smoking-related behaviours (such as use of NRT) and participants' recall and comprehension of their risk assessment.

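### Blinding is required of the six-month caller but not of the one-week caller, so the self-reported one-week cessation outcome may be taken by someone who knows the arm

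*Protocol article*

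**What the plan says.** The assessor rules stand in adjacent paragraphs of the Procedure section of the protocol article. For Telephone call 3 the rule is: "A member of the research team who did not deliver the intervention will assess self-reported seven-day smoking cessation". For Telephone call 4 it is: "This telephone call will be made by a member of the research team who did not deliver the intervention and who is blind to allocation".

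The outcome definitions differ too. For one week: "Self-reported smoking cessation will be assessed at one week following receipt of the CD risk assessment". For six months: "self-reported smoking status will be verified biochemically", with a cotinine threshold. Saliva collection is described only under Telephone call 4: "Saliva samples will be collected via post in those who report seven day smoking abstinence, to allow cotinine validation".

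The abstract names seven-day abstinence at both time points as the secondary outcomes. The Statistical analysis section compares both between arms with a confidence interval and a chi-squared test. It also treats every participant as a smoker on the secondary cessation outcomes unless abstinence has been confirmed biochemically, and it does not limit that rule to six months.

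The Concealment section states that the counsellor and the participant know the arm after assignment. It says nothing about the one-week caller.

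**The concern.** The wording for the six-month call treats two things as separate: having had no part in giving the intervention, and not knowing the arm. The one-week call asks only for the first. A caller who knows the arm may, without intending to, probe differently or resolve a doubtful answer differently in the two arms.

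Of the two secondary cessation outcomes, the one-week outcome has less protection against this. Six-month abstinence has a blind caller and a cotinine check; the one-week outcome is given neither. A between-arm difference at one week would then be harder to read as a difference in smoking. At stake is the credibility of one secondary result, not the trial's main conclusion.

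**Working it through.** No stated figure bears on this point, so the check compares the text.

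**1. The safeguards for each outcome**

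| Safeguard | One week (call 3) | Six months (call 4) |
|---|---|---|
| Caller separate from the person giving the intervention | Required | Required |
| Caller blind to arm | Not stated | Required |
| Biochemical check | None described | Cotinine, in those reporting seven-day abstinence |
| Participant blind | No | No |
| Outcomes taken | Secondary: seven-day abstinence | Primary: quit attempt; secondary: seven-day abstinence |

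**2. Could someone who knows the arm meet the one-week rule?** Yes. Under Randomisation, Procedure, the coordination team gets the allocated group back from the statisticians. Under Telephone call 1, the trial co-ordinator sends out the results booklet, whose content differs by arm. Counselling is the research counsellor's task. Coordination staff could therefore satisfy the one-week rule while knowing the allocation. No section assigns the one-week call to them, and none rules them out.

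**3. Could the call itself reveal the arm?** Possibly. The Additional outcomes section places questionnaires in calls 1, 3 and 4 and adds an assessment of "participants' recall and comprehension of their risk assessment". It does not say which call carries the recall items. Call 1 comes before the results booklet, so that leaves call 3, call 4 or both. A participant who describes a gene result tells the caller the arm.

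**4. How does the analysis rule treat the one-week outcome?** There are two readings:

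- Analysed as self-report, as its definition says, the outcome depends on the answer recorded at call 3, and the gap in step 1 applies.
- Analysed under the verification rule as written, nobody can count as abstinent, because no one-week sample is described. The proportions are 0/n in the DNA arm and 0/n in the comparison arm, so the difference is 0 − 0 = 0 and the odds ratio is 0/0, which is undefined. The outcome carries no information.

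The second reading removes the scope for assessor bias, but only by emptying the outcome. It is unlikely to be what was meant, and the text needs amending under either reading.

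**5. Size.** An estimate of the bias would need the true one-week abstinence rate and the rate at which answers are misrecorded in one arm. The document gives neither, so any figure would only restate the assumptions put into it. None is offered.

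**The case against.** The strongest reply is that silence is not permission. The article does not say that the one-week caller knows the arm. It already excludes the person with the closest stake, and staffing detail is often left to the full protocol. This stands in part: the callers may well have been blind, and one clause would settle it. But the contrast between adjacent paragraphs is a stated difference in the rule, so it cannot be put down wholly to condensation.

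Second, the Fidelity checks section says that all calls are recorded and that a random sub-sample is transcribed. A recording can show how a question was put and what was answered, so a reader should not infer that nothing could ever detect the problem. The stated purpose, however, is fidelity to the clinical protocol. It is a partial check and not blinded assessment of the outcome.

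Third, participants know their arm, so a blind caller leaves their own reporting bias in place. That is correct and limits what the change can achieve. It does not remove the reason for blinding the caller, which the trial itself accepts at six months.

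Fourth, the consequence is limited, because the primary outcome and cotinine-checked abstinence both come from the blinded call. This stands in full.

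**Conclusion.** The point holds as a gap in one safeguard for one of the two secondary cessation outcomes. The protocol allows, but does not say, that the one-week caller knows the arm, so assessor bias is possible and not shown. A reader might infer that one-week results were in fact collected unblinded, or that they are biased by some stated amount; the document supports neither. The primary outcome, six-month abstinence and the sample size are untouched.

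The conclusion assumes that the one-week outcome is meant to be analysed as self-report. Separately, and whoever makes the call, the one-week definition and the verification rule in the Statistical analysis section cannot both be applied as written.

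**What to change.** 1. Under Telephone call 3, require the same caller as for Telephone call 4: someone who took no part in the intervention and does not know the arm.
2. Have the cessation answer recorded before any item that may reveal the arm, such as recall of the risk assessment.
3. If a call cannot be blind, or if calls already made were not, report the one-week outcome as unblinded, unverified self-report.
4. Reconcile Telephone call 3 and the one-week outcome definition with the Statistical analysis section. Either limit the verification rule to six months and say that one week is analysed as self-report, or describe verification at one week.

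The cost is small but not shown to be nil. A caller who learns the arm at one week should not make that participant's six-month call, which complicates scheduling, and the article gives no staff numbers from which to judge the burden. Items 2 to 4 need wording, or a fixed item order; only adding one-week verification under item 4 would mean extra samples. No sample-size figure changes. Participant reporting bias would remain and should be acknowledged when the one-week result is interpreted.
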